**5.2. Use of co-intervention (if applicable)**

In case of discomfort the CVI processor can be turned off or removed from the patient's head at any point, instantly stopping the stimulation of the vestibular system.

**5.3. Escape medication (if applicable)**

- Not applicable -

## 6. INVESTIGATIONAL PRODUCT

### 6.1. Name and description of investigational product

See chapter 5.1 for a general description of the investigational product and see section D of the standard research file (the IMDD) for a more detailed description.

### 6.2. Summary of findings from non-clinical studies

Extensive animal testing has been conducted to gain general knowledge on vestibular stimulation and to test vestibular implants. This research identified electrical stimulation as an effective means of stimulating the vestibular system in animals already in the 1960's. Currently, the main focus of animal research is directed towards thoroughly investigating the effects of electrical stimulation parameters on vestibular responses, focusing on vestibular-ocular responses, as well as orientation percepts and postural responses.

No non-clinical studies were performed with the CVI research devices. All the results were obtained from clinical studies, conducted over the last 13 years. Therefore there is no summary of findings from non-clinical studies specific to this investigational product.

### 6.3. Summary of findings from clinical studies

Clinical research on CVI's within the Geneva-Maastricht group started in 2007 with implanting a CI device with a single channel VI. After development of additional surgical techniques, and successful intra-operative vestibular stimulation, the first CVI's containing multichannel VI's were implanted in 2012. The possibility of acute hearing preservation and the feasibility of additional surgical tools were presented. It was shown that the CVI is a safe and effective way of stimulating the vestibular system, even in a heterogeneous patient population. Relevant functional benefits were shown by restoring the VOR, improving vision during walking and by restoring high frequency DVA.

Recently the preliminary findings of a prolonged vestibular stimulation trial conducted in the USA by the group of Della Santina were published. In this trial a VI-only device is being tested on patients without severe SNHL. They have reported follow-up results on their first four patients after several years of continuous daily stimulation. Their results show stable restoration of the VOR and positive subjective outcomes. Alongside this they have not reported any adverse effects of the prolonged stimulation. With the VertiGO! trial we aim to fill research gaps which will not be answered within the Della Santina trial, conducting a randomized and more rigorous trial focused on the first weeks of prolonged stimulation, including CI functionality during vestibular stimulation and general device safety focusing on a different patient population (BV and severe SNHL).

### 6.4. Summary of known and potential risks and benefits

#### 6.4.1. *Risks related to the CVI implant*

MED-EL (manufacturer of CI systems) has established and maintains a documented and effective Quality Management System in accordance with ISO 13485 and applicable regulatory requirements. MED-EL's Quality Management System (QMS) outlines the processes necessary to fulfil national and international

requirements for medical devices. The CVI is a device developed for research and is therefore not a CE marked medical device, nor is it intended to be put on the market.

Production of the CVI research implants takes place in environmentally-controlled cleanrooms for products that are distributed in sterile condition. Electrostatic-sensitive assemblies and subassemblies are constructed in ESD-protected areas. Qualified and calibrated equipment is used in production and for testing/verification purposes. MED-EL implements procedures to ensure that if the work environment can adversely affect product quality, it is adequately monitored and controlled. Personnel involved in the manufacturing of research devices are adequately trained for research device production and generally trained according to MED-EL's quality management system.

Patients will be informed, that with this implant (just as with many other implantable devices in medicine), the patient should not undergo MRI scanning. The implant has not been tested for MRI safety and is labeled as MRI Unsafe (see Annex IV of the IMDD, section D of the standard research file). If there are medical reasons for the patient to undergo MRI examination, the patient is required to first contact the ENT department of the MUMC+ to discuss the risks and the possibilities.

A more detailed description of the device related risks can be found in section D of the standard research file (the IMDD).

#### 6.4.2. *Risks related to the AMP*

The AMP is a research use only device designed to allow simultaneous stimulation of the SCCs and the cochlea. It will be used under supervision of medical personnel while the patient is free to move around and perform routine daily activities. The audio processor part of the AMP is equivalent to a standard CI processor. The motion processor is added onto this, following the same design principles and stimulation restrictions as a CI processor to ensure safe stimulation of the CVI implant. To perform the fitting for the motion-processing part of the AMP, the AmpFIT software package is used, specifically designed to work together with the AMP.

This will be the first time the AMP will be used to drive a CVI implant in humans. To minimize any potential risks, the AMP will only be used by the patient when the patient is under supervision inside the hospital. Also, the patient is able to stop the stimulation of the CVI implant by the AMP at any point by turning it off or taking off the device. This immediately stops any current from passing through the CVI implant.

A more detailed description of the device related risks can be found in section D of the standard research file (the IMDD).

#### 6.4.3. *Risks related to CVI surgery*

Until now, none of the 13 patients that were implanted with a CVI by the Geneva-Maastricht group suffered from any surgical complications related to the well-defined surgical approach. Risks of surgical implantation are low. Surgery is derived from a frequently performed surgical intervention which has proven to be safe: cochlear implantation. The main risk of CVI surgery is damage to the sensory structures in the cochlea and the vestibular organ, resulting in hearing loss and loss of vestibular function. These risks are minimized by only implanting patients with severe SNHL in the ear to be implanted and

with only minimal vestibular function remaining. Alongside this, the potential hearing loss is compensated for by the CI functionality of the CVI.

The inclusion criteria imply that three types of patients are eligible for participation: patients with BV and bilateral deafness who have an indication for reimbursement of unilateral cochlear implantation (in the Netherlands), patients with BV and unilateral deafness for whom cochlear implantation is not insured (in the Netherlands) and patients with BV and bilateral deafness who have already received a CI in the contralateral ear. Since the CVI is a combined device, combining a VI- and a CI-part in one device (Figure 5), hearing will be restored on the implanted side. Therefore in the first group (bilateral deafness), the CVI will be implanted instead of a regular CI implant during their cochlear implantation in the same surgical field, without additional incisions. The two other groups (unilateral deafness and bilateral deafness with already one CI implanted) will undergo surgery specific for this trial, but will also benefit from the CVI implantation: their hearing will most likely improve .

#### 6.4.4. *Risks of explanting the CVI*

Until now, none of the previous 13 patients implanted with a CVI, needed to be explanted. However, since the CVI is a derivative of the CI, the reasons for explanting (e.g. infection) and the associated risks should be equal to that of a CI. It is shown that although CIs are not often explanted, it is a safe procedure with low risks . The only risks are related to the explant surgery itself: infection and bleeding. Since the CVI is only implanted in organs which have a complete or near total loss of function, there will be no substantial risk of damaging these organs. Another reason for explanting might be due to device failure, followed by implanting a new device (which could be either a CVI or a CI). This will not be performed for patients as part of this trial, and it should be noted that explanting and implanting a new device is not a goal. The concept of a CI, and by analogy also a CVI, is that it can provide lifelong stimulation.

#### 6.4.5. *Risks of electrical stimulation of nerves*

From research and years of experience with cochlear implantation it is known that long-term stimulation of nerves does not lead to unwanted neural damage, as long as current is kept below a safe level and the right materials are used . In our project, a modified CI is used, which implies a well-tested, daily used device with standard electrodes. It is called “modified” since it has four arrays of electrodes instead of one. The use of multiple cochlear electrode arrays (e.g. “split array”) is a known clinical procedure that can be applied in certain cases where significant cochlear calcification requires more than one cochlear insertion site to reach the cochlear nerve. Previous trials of the Geneva-Maastricht group already demonstrated that acute responses to VI stimulation can be obtained after an extended time (at least several years), without damaging the nerves .

#### 6.4.6. *Risks related to adjusting the settings of the CVI*

Adjusting the settings of the CVI results in changing the previous stimulation state of the vestibular nerves. Research shows that this can lead to dizziness . By performing the adjustments of the stimulation settings in a gradual fashion, utilizing the adaptive capabilities of the human brain, this dizziness can be kept to a minimum. Additionally, due to the change in balance perception, there is a potential risk of falling. The current set-up of the trial takes these risks into account and attempts to minimize them by

scheduling 4 full days to adjust and fine-tune the stimulation settings. This fitting period specifically focusses on preventing side effects as much as possible. When applied in previous research from the Geneva-Maastricht Group, this way of adjusting the stimulation settings resulted in only mild and temporary side effects (e.g. tiredness).

It has also been shown that side effects decrease with increasing use of the CVI. Previous experiments with a patient who received a CVI showed that the duration of unwanted nystagmus which can cause dizziness decreased substantially within several on-off cycles. This suggests the potential of reaching a situation of dual-state adaptation, where the patient is able to switch the CVI on and off without any side effects.

Since this will be the first time that the CVI will be used for prolonged stimulation while the patient performs daily tasks, there is a chance for side effects such as nausea to occur during this period, in combination with certain stimulation algorithms. Also there is a potential risk of falling due to changes in balance perception. When they occur, these side effects might be reduced by optimizing stimulation settings. These side effects can always be stopped by turning off the AMP or taking off the device. The risks related to these side effects are minimized due to the vestibular stimulation only being applied under supervision within the hospital.

#### **6.4.7. Benefits of the CVI**

Patients who receive a CVI will in any case benefit from the cochlear part of the device: their hearing will most likely be improved. If vestibular stimulation via a CVI works as is hypothesized and such a device would be available for long term use, it can lead to a substantial quality of life improvement for patients. Disabling symptoms associated with BV would be reduced and a patient's ability to participate in society would be improved. These benefits will however not currently be available for patients, since the AMP is a research-only device, and will only be used for research purposes under supervision in the hospital. This research can lead to further development of the concept of a VI, potentially leading to a device which will be available for patients to use as part of standard clinical care.

#### **6.5. Description and justification of route of administration and dosage**

- Not applicable -

#### **6.6. Dosages, dosage modifications and method of administration**

The CVI implant is implanted inside the cochlea and the SCCs, with the receiver coil being placed subcutaneously. The AMP is connected to the implant via a sending coil placed on the skin on top of the receiver coil and is held in place by magnetic force. The audio processor part of the AMP is placed behind the ear and the motion processor part of the AMP hangs on a cord around the patient's neck.

#### **6.7. Preparation and labelling of Investigational Medicinal Product**

A full description of device production and examples of labelling can be found in section D of the standard research file (the IMDD).

**6.8. Drug accountability**

The CVI implants will be delivered by courier to the hospital, in analogy with the standard delivery of CI implants. The AMP devices will be delivered by the manufacturer to the research personnel, and will stay inside the hospital until the end of the trial, at which point they will be returned to the manufacturer.

## **7. NON-INVESTIGATIONAL PRODUCT**

### **7.1.Name and description of non-investigational product(s)**

Outside of the VI fitting period and the prolonged stimulation period when the patient is under supervision in the hospital, the patient will use a regular CI processor to drive their CVI implant. This processor is the CE-marked MED-EL Sonnet 2 audio processor. Being the latest version of the MED-EL CI processor product line, it utilizes advanced hearing technology to give optimal sound quality. Supplementary documents describing the Sonnet 2 audio processor can be found in section D6 of the standard research file.

Utilizing the standard MED-EL MAESTRO software package the three electrodes placed in the SCCs will be turned off. The deactivation of electrodes is part of the normal CI fitting procedure, performed when for example faulty electrodes are detected or when electrodes are not situated in the cochlea due to the electrode array not being fully inserted into the cochlea. By deactivating the vestibular electrodes, the CVI implant operates exactly like a regular CI implant with its 3 most basal electrodes turned off.

### **7.2.Summary of findings from non-clinical studies**

- Not applicable -

### **7.3.Summary of findings from clinical studies**

- Not applicable -

### **7.4.Summary of known and potential risks and benefits**

- Not applicable -

### **7.5.Description and justification of route of administration and dosage**

- Not applicable -

### **7.6.Dosages, dosage modifications and method of administration**

The Sonnet 2 audio processor is worn behind the ear with the sending coil being placed on the skin on top of the receiving coil of the CVI implant, held in place by magnetic force.

### **7.7.Preparation and labelling of Non Investigational Medicinal Product**

Labelling will be as standard for this CE marked device.

### **7.8.Drug accountability**

- Not applicable -

## 8. METHODS

### 8.1. Study parameters/endpoints

The study parameters are divided into main study parameters and secondary study parameters. Main study parameters include all objective outcomes included in the trial. Secondary study parameters include all subjective outcomes. An overview of the outcome parameters and endpoints in relation to the objectives is given in table 6.

#### 8.1.1. Main study parameters/endpoints

The primary objective is assessing the efficacy of the CVI in restoring vestibular function. This will be measured by using a set of vestibular tests, of which DVA will be the main outcome parameter. The tests that will be performed observe two vestibular-related reflex pathways: VOR (gaze stabilization) and VSR (postural balance). The VOR tests consist of the DVA test, the functional head impulse test (fHIT), the 3D video head impulse test (3D HIT) and the torsion swing test. All these tests quantify the VOR at different frequencies and at different levels of functionality. The VSR is observed based on gait and balance tests, looking at the full body response to vestibular stimulation on a functional level. Besides these tests, also the threshold of the perception of movement will be measured using the perception platform.

The main comparison will be made between the measurements done during baseline testing (VI-OFF) and the measurements done during the prolonged stimulation period (VI-ON) (see chapter 2). This will give a

Table 6: Overview of VertiGO! objectives, goals, endpoints and outcome parameters

| Objective |                       |    | Goal                          | Measurement points                                   | Outcome parameters |      |                                                                 |
|-----------|-----------------------|----|-------------------------------|------------------------------------------------------|--------------------|------|-----------------------------------------------------------------|
|           |                       |    |                               |                                                      | Type               | Test |                                                                 |
| Primary   | Prolonged daily stim. | 1a | Overall efficacy              | VI-OFF (baseline) vs VI-ON (stim. weeks)             | Prim.              | Main | DVA                                                             |
|           |                       |    | Adaption to stimulation       | VI-ON (start stim. weeks) vs VI-ON (end stim. weeks) |                    | Aux. | fHIT, 3D HIT, Torsion Swing, Gait analysis, Perception platform |
|           |                       | 1b | Safety                        | stim. weeks                                          | Sec.               |      | Questionnaires, Interviews                                      |
|           |                       |    |                               |                                                      |                    |      | (S)AE's                                                         |
|           |                       | 1c | Efficacy of 3 stim. types     | VI-ON (week 1) vs VI-ON (week 2) vs VI-ON (week 3)   | Prim.              | Main | DVA                                                             |
|           |                       |    |                               |                                                      |                    | Aux. | fHIT, 3D HIT, Torsion Swing, Gait analysis, Perception platform |
| Secondary | Rehab.                | 2a | Rehab. program                | stim. weeks                                          | Prim.              |      | Gait analysis                                                   |
|           |                       |    |                               |                                                      | Sec.               |      | Questionnaires, Interviews                                      |
|           | CI                    | 2b | Interaction between CI and VI | CI-ON/VI-OFF (baseline) vs CI-ON/VI-ON (stim. weeks) | Prim.              |      | Aided CNC, SPIN, vestibular test                                |
|           |                       |    | CI as part of VCI             | CI-ON (up to 5 years)                                | Sec.               |      | Questionnaires, Interviews                                      |
|           | Long term             | 2c | Acute efficacy                | VI-ON (up to 5 years)                                | Prim.              |      | Subset of vestibular tests                                      |
|           |                       |    |                               |                                                      |                    |      |                                                                 |

general result on the efficacy of prolonged vestibular stimulation. A further statement of CVI efficacy will be made based on the response to stimulation throughout the different prolonged stimulation weeks. Therefore the VOR tests will be performed several times during the prolonged stimulation weeks. A comparison of these results will yield statements on potential adaptation effects (e.g. habituation to receiving information via the CVI, increase/decrease in response gain and potential increase in VOR alignment). The same set of VOR and VSR tests measured throughout the prolonged stimulation weeks will also serve as parameters for comparing the different stimulation algorithms.

A subset of the vestibular tests will be performed during the annual follow-up visits. These parameters will be used to quantify the stability of acute stimulation and implant functionality over a clinical follow-up period of 5 years.

The functionality of the CI-part of the CVI will be assessed with an aided consonant-nucleus-consonant (CNC) hearing test. This will be done by making the comparison between aided CNC scores using the regular CI processor and aided CNC scores using the CVI processor (the AMP) with both CI and VI part active. During the CI follow-up visits speech in noise (SPIN) tests will be performed as part of the auditory follow-up test set to allow for evaluation of the CI part of the CVI implant and compare this outcome with CI performance of a regular CI implant.

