### 2.2. Secondary objectives

*a. To develop a rehabilitation program for VI recipients*

It is expected that patients will benefit from physiotherapeutic rehabilitation during prolonged VI stimulation by improving its functional outcome.

*b. To evaluate the interaction between vestibular and cochlear nerve stimulation*

It is expected that there will be interaction between the stimulation of the vestibular organ and the cochlea. The extent and clinical relevance will be characterized.

*c. To evaluate acute VI performance across several years*

It is expected that the CVI will induce stable VOR responses during acute stimulation over time. The clinical follow-up of the implanted patients will bring new insights for future research.

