#### ***CI follow-up visits***

For the regular clinical CI rehabilitation care the patient is asked to visit the hospital at regular intervals for a check-up (see chapter 3, table 1). During these visits of around 2 hours another 4 hours are added on average to also perform a VI check-up. This VI check-up will include tests similar to the tests which were performed during the fitting week and/or prolonged stimulation period. During these tests the VI electrodes will be stimulated and response to stimulation will be characterized. The main purpose is to test whether electrode impedances and vestibular responses remain constant over time. Also during these visits additional hearing tests and questionnaires will be administered.

At the 1, 2 and 5 year follow-up visits a CBCT scan will be made to assess if any change occurs on the position of the electrodes inside the SCCs and the cochlea. This information can then be linked to device efficacy and it can be used to assess potential causes of problems with the CVI if they occur. It will also allow for evaluating the benefit from postoperative scanning in the follow-up of the CVI.

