### 10.1. Primary study parameter(s)

The main comparison of the primary outcome parameters will be between the conditions of VI-OFF and VI-ON. The comparison between these two conditions will be done via an intention-to-treat approach using a Wilcoxon signed-rank test (non-parametric) due to the small sample size and the unlikelihood of being able to proof normality. For this analysis, data from the baseline testing, the prolonged stimulation period and the long-term follow-up will be used. To compare between the different stimulation algorithms, only descriptive statistics will be applied. The lack of statistical power caused by the small sample size does not allow for a multilevel repeated measures analysis of the data.

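### Objective 2c (long-term acute efficacy) has no specified same-visit VI-OFF reading, yet section 10.1 puts follow-up data into the VI-OFF versus VI-ON test

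*Protocol*

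**What the plan says.** **Measurement points.** In Table 6 (section 8.1.1) the row for objective 2c has a goal labelled acute efficacy, a subset of the vestibular tests as outcome, and "VI-ON (up to 5 years") as its only measurement point. The overall-efficacy row of objective 1a names both conditions: "VI-OFF (baseline) vs VI-ON (stim. weeks"). The row on CI/VI interaction (2b) also names both.

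**Purpose of the follow-up data.** Section 2.2 states the expectation for 2c: "It is expected that the CVI will induce stable VOR responses during acute stimulation over time". Section 8.1.1 says the follow-up subset will "quantify the stability of acute stimulation and implant functionality over a clinical follow-up period of 5 years".

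**Conduct at follow-up.** Section 8.3.6, CI follow-up visits, says the tests resemble those of the fitting week, the stimulation weeks, or both, and continues: "During these tests the VI electrodes will be stimulated and response to stimulation will be characterized". It adds: "The main purpose is to test whether electrode impedances and vestibular responses remain constant over time". It mentions no unstimulated run.

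**Analysis.** Section 10.1 compares VI-OFF with VI-ON by a Wilcoxon signed-rank test and says that "data from the baseline testing, the prolonged stimulation period and the long-term follow-up will be used".

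**Where VI-OFF is described.** Section 8.3.6, Baseline testing, places the VI-OFF control for all vestibular outcomes on the baseline day. It keeps the gap to the stimulation weeks to a few months so that the control stays valid. The Sunday perception tests before each stimulation week are also done without the VI.

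**Processor.** Section 8.3.6 (CI rehabilitation) and legend C to Table 1 confine active use of the motion processor to the fitting and prolonged stimulation periods. Sections 7.1 and 13.1.8 say a regular CI processor drives the implant at other times.

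**The concern.** An efficacy statement at year 1 to 5 needs the difference between stimulated and unstimulated performance at that time. A head-impulse, chair or treadmill DVA reading with the VI on reflects natural function, compensation and practice as well as the implant. Table 5 (section 4.2.1) admits patients with some remaining function, for example bilateral horizontal head-impulse gain up to 0.6 under criterion A.

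If only the stimulated reading is followed, further natural loss would look like a failing implant. Better compensation or test practice could hide a real decline. If those readings enter the section 10.1 test against the baseline VI-OFF value, the same drift reaches the on/off comparison of the main study parameters. A VI-OFF run not taken at the visit cannot be recovered later.

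**Working it through.** **1. The plan's own figure.** No figure is given for 2c. The only stated effect is for the on/off DVA comparison in section 4.4: VI active 0.065 (SD 0.061), VI inactive 0.205 (SD 0.066), effect size 2.20, minimal N of 5.

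- Difference: 0.205 − 0.065 = 0.140 logMAR.
- SD of the difference, with an unstated correlation r taken as 0.5: √(0.061² + 0.066² − 2 × 0.5 × 0.061 × 0.066) = √0.004051 = 0.0636.
- Effect size: 0.140 / 0.0636 = 2.20, as stated.
- Noncentral-t power, corrected for the asymptotic efficiency of the Wilcoxon test (3/π for normal data, or the minimum 0.864): 0.783 or 0.686 at n = 4, and 0.932 or 0.878 at n = 5. So N = 5 reproduces on that approximation.

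This does not bear on 2c. It only supplies 0.140 logMAR as a scale.

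**2. Age of the comparator.** CI rehabilitation starts about 1 month after implantation, and the baseline day falls 6 to 24 months after that start. Baseline is therefore about 7 to 25 months after implantation. Follow-up runs to 5 years (60 months) after implantation. At year 5 the baseline VI-OFF reading is 60 − 25 = 35 to 60 − 7 = 53 months old (about 2.9 to 4.4 years), against the few months the protocol allows before the stimulation weeks.

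**3. Effect of drift (illustration).** Assume that the implant effect stays at 0.140 logMAR and that the unstimulated level worsens additively by d. The documents give no value for d.

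- Change in the VI-ON-only series: d
- Baseline VI-OFF minus late VI-ON: 0.205 − (0.065 + d) = 0.140 − d
- Same-visit VI-OFF minus VI-ON: (0.205 + d) − (0.065 + d) = 0.140

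| Assumed d | VI-ON change | Apparent loss (d / 0.140) | Baseline OFF − late ON | Same-visit OFF − ON |
|---|---|---|---|---|
| 0.02 | 0.02 | 14% | 0.12 | 0.140 |
| 0.05 | 0.05 | 36% | 0.09 | 0.140 |
| 0.10 | 0.10 | 71% | 0.04 | 0.140 |
| 0.14 | 0.14 | 100% | 0.00 | 0.140 |

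In the other direction, if the implant's contribution falls by 0.03 and practice gains 0.03, the VI-ON series shows no change.

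**4. Which tests are exposed.**

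- *Exposed:* tests driven by head or body movement (head impulse, chair, DVA).
- *Partly protected:* DVA includes a static acuity reading in the same test (section 8.3.1), so a change in vision cancels if DVA is expressed relative to it. Section 4.4 did this for the earlier data. The protocol does not state it for the trial data. A change in residual reflex function does not cancel.
- *Not exposed:* impedances and responses evoked purely by electrical stimulation without head movement.

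**5. Which tests are run at follow-up.** This cannot be settled from the readable text. The follow-up paragraph allows tests like those of the stimulation weeks, which include movement tests. The processor statements point to direct electrode stimulation only, since the motion processor is what turns head movement into stimulation (section 5.1.2). Read literally, section 13.1.8 would even exclude vestibular stimulation at follow-up.

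**The case against.** **2c is about stability, not on/off efficacy.** Sections 2.2, 8.1.1 and 8.3.6 all ask whether stimulated responses stay constant, and a VI-ON series is a natural measure of that. Table 6 also uses VI-ON against VI-ON for adaptation and for the comparison of stimulation types. This largely stands for evoked responses. It does not cover the efficacy label or the entry of the data into an on/off test. The other VI-ON comparisons also lie within a few weeks, not years.

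**Follow-up may consist only of evoked responses.** The processor restriction makes this plausible, and such data need no VI-OFF run. But then they do not measure functional efficacy and have no place in the section 10.1 comparison, so the text still has to change.

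**Other checks exist.** VEMPs are meant to observe residual function during the trial, and the static DVA reference handles vision. Both help, but a VEMP is not an unstimulated reading of the head-impulse, chair or DVA test.

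**Pairing belongs in the analysis plan.** How values are paired may be left there. Whether an unstimulated run is taken at the visit is a matter of conduct, and the protocol has to fix it.

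**Stronger readings to avoid.** A reader might infer that no VI-OFF run takes place at follow-up. Table 1, which lists tests by visit, is illegible in the available copy, so one can say only that the readable text specifies none. A reader might also infer that the baseline day is the sole source of VI-OFF data. The Sunday perception tests are done without the VI, and Table 3 appears to schedule DVA with the CI alone and with the full CVI in one fitting-week session.

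**Conclusion.** The concern holds in a limited form. The readable protocol specifies no same-visit VI-OFF reading for 2c, calls the goal efficacy, and adds follow-up data to an on/off test whose described comparator is, for most vestibular outcomes, about 3 to 4.5 years old at year 5. That conflicts with the protocol's own reason for keeping the control close in time.

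The consequence is confined to movement-based tests in the follow-up subset. Its size is unknown: every drift value above is assumed, as is additivity of natural and implant function, and section 13.2 expects almost no residual function in these patients. The documents do not support a claim that the 2c result will be wrong, or that changes in vision go uncontrolled.

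Objective 2c is secondary and section 10 declares the trial exploratory. This is a modest, inexpensive correction.

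**What to change.** 1. **Reconcile the text.** Bring section 8.1.1, Table 6 and the follow-up paragraph of section 8.3.6 into line with the processor statements in section 8.3.6 (CI rehabilitation), section 7.1 and section 13.1.8. State which tests are done at follow-up and which processor or software drives them.
2. **If any movement-based test is in the subset,** change row 2c to *VI-ON vs VI-OFF at the same visit (up to 5 years)*. Add one unstimulated run of that test at the visit and report the within-visit difference over time.
3. **If only evoked responses and impedances are measured,** rename the 2c goal to stability of the stimulated response. No VI-OFF run is then needed.
4. **In either case,** exclude from the section 10.1 on/off test any long-term VI-ON value without a same-visit VI-OFF reading.

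**Cost.** By the times in section 8.3.1, DVA takes about 10 minutes, 3D HIT about 20 and torsion swing about 10: 10 minutes for DVA or torsion swing alone, up to 10 + 20 + 10 = 40 for all three. That is at most 40/240 = 17% of the roughly 4 hours (240 minutes) already added per visit. Habituation adds to this: section 8.3.6 cites about 30 minutes at first stimulation and less later. Switching between conditions within a visit also carries some risk of carry-over. Items 1, 3 and 4 are wording changes only.
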